# **Multistate Transition Model:**

Our data involves 3 processes: 1) whether patients received tPA/DNase therapy or not, 2) whether patient’s chest tube was deemed clogged vs patent, after appropriate steps taken to unclog a tube, and 3) whether the chest tube ± tPA/DNase was considered a treatment failure, requiring additional invasive procedures. Patients could experience a clogged tube but continue to have ongoing treatment in the form of antibiotics, ongoing drainage, and possible tPA/DNase (as opposed to treatment failure). Patients could transition between states of patent, vs clogged and tPA/DNase free vs tPA/DNase therapy, but if a patient was considered a treatment failure, this state was defined as an absorbing state/terminal state.

Considering these three processes yielded twelve possible states, or categories (see above): 1) patent chest tube with treatment successful, no tPA/DNase (in the past 24 hours), 2) clogged chest tube with treatment successful, no tPA/DNase, 3) patent chest tube with tPA/DNase, treatment successful, 4) clogged chest tube with treatment successful, with tPA/DNase, 5) patent chest tube with ongoing treatment, no tPA/DNase 6) patent chest tube with tPA/DNase with ongoing treatment, 7) clogged chest tube with ongoing treatment, no tPA/DNase 8) clogged chest tube with tPA/DNase with ongoing treatment, 9) patent chest tube with failed treatment, no tPA/DNase 10) patent chest tube with tPA/DNase with failed treatment, 11) clogged chest tube with tPA/DNase with failed treatment and 12) clogged chest tube with failed treatment.

We define four ordinal levels of status based on each category and each patient’s status will be assessed daily from randomization to treatment success, or failure. At any one point, a patient can be within one state, or category, and reaching any absorbing group, defined as treatment success, or treatment failure (groups 1 or groups 4) results in a terminal state with no further transitions possible.

Definition of States**:***Absorbing state* a terminal state, in which the probability of leaving that state is zero. 

*Treatment Successful* notes inpatient effusion management is complete. Chest tube can be removed, and patient could be discharged from a pleural infection standpoint. This does not include those discharged with a chest tube in place for ongoing management.

*Treatment failed* notes the patient needs an additional procedure for management of their pleural space (e.g., additional chest tube, surgery, etc.).

*Patency of tube* is assessed by the presence of tidaling and/or evidence of ongoing drainage output (*clogged vs. patent)*.

# **Statistical Considerations**

*Objective and sample size justification*

This is an open label, randomized, multicenter study of the application of flushing for the treatment of pleural space infection among hospitalized patients requiring chest tube drainage. Patients will be enrolled and randomized with a 1:1 ratio to two treatment groups: (1) 20 mL of sterile saline catheter flushing every 6±2 hours with the application of continuous -20 cm H2O suction (2) as needed saline flushing for blockage with the application of continuous -20 cm H2O suction. After enrollment, daily drain patency and criteria for drain removal will be measured and documented. The primary objective of this study is to evaluate the impact of regular chest tube drain flushing on the length of time to catheter removal for patients admitted with pleural space infection who require thoracostomy for their management. Chest tube removal due to chest tube dislodgement or malposition, or “kinking”, and if the patient is deceased with a chest tube in situ, are considered competing risks and will be analyzed as such.

The secondary objective of this study is to evaluate the impact of regular chest drain flushing on the length of hospitalization for patients, radiographic improvement on chest imaging, the need for additional pleural interventions, and associated complications of chest tube management.

Previous studies have shown a varying number of days to chest tube removal based on etiology, with a mean of 7.6 days (SD: 1.53) in no regular flush populations in a study of 98 patients with infected pleural space (Cafarotti). There is limited data with only one small study reporting median days to chest tube removal (5 days (3-7) in a study of 36 patients with no-flush strategy) (Horsley). Assuming a non-normal distribution, with data skewed to the right, we estimated a median of 6 days to chest tube removal. Assuming a difference of 1 day (24 hours), earlier chest tube removal in the intervention (6 days in the SOC group and 5 days in the intervention group) is a clinical meaningful difference to detect. The sample size is calculated from a two-sided Wilcoxon Rank-Sum test at a 0.050 significance level with a standard deviation of 1.5. Group sample sizes of 38 in each arm achieve 80% power to detect a median difference of 1. The sample size estimation is based on a 2000 Monte Carlo simulation assuming samples from a range of distribution such as Gamma, Lognormal, and Gumbel distributions. Assuming a 10% withdrawal rate and 15% intrapleural enzyme therapy failure (which can prevent reaching the primary endpoint), we plan to enroll 96 Participants (with randomization performed in a 1:1 ratio). To avoid an unbalance in randomization among groups, randomization will be stratified by intrapleural enzyme therapy use.

The main analysis for the outcome will be performed according to the intention-to-treat principle; all the participants with an observed outcome will be included in the analysis according to their assigned trial group.

*Analysis plans*

Continuous variables will be summarized using the mean (SD) or median (range), as appropriate. Frequencies and percentages will be used to summarize categorical variables. The student t-test or the Wilcoxon test will be used to compare continuous variables between two different groups. The chi-square test or Fisher’s exact test will be applied to assess the association between two categorical variables such as complications by treatment.

The Wilcoxon rank sum test will be used to compare time from randomization (within 24 hours of chest tube placement) until time to chest tube removal between two arms among patients who achieved successful chest tube removal.

For the primary endpoint, if data is normally distributed, data will be analyzed via students t-tests comparing time from randomization until time to chest drain removal between the two arms, among patients who received successful chest drain removal. For non-normally distributed data, the Wilcoxon rank sum test will be used for this comparison. If a chest drain’s removal was due to a competing risk (chest drain dislodgement, malposition or “kinking”, patient died with chest drain in situ), a competing risk time-to-event regression model will be applied.

In addition to the primary endpoint of interest, we are interested in the comparison of the time to the failure of therapy/drainage between two arms. For the time to the failure of therapy/drainage analysis, Cox regression with the adjustment of covariates of interest will be used in all enrolled subjects, including patients who reached successful chest tube removal and those with failure of therapy/drainage and need for additional interventions. The cumulative failure of therapy/drainage curve will be calculated from the Kaplan-Meier method and compared using the log-rank test. For the exploratory study, we will apply Markov ordinal longitudinal proportional odds state transition model to analyze our interventions into impact on the process of chest tube drainage to successful outcome or failure. This model will provide further characterization of intervention and control arms with regards to state of chest drain and state of patient among all populations, including those with chest drain failure, to characterize differences among these groups.

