# **Background**

Pleural effusions are a frequent complication of acute pulmonary infections and can impact patient morbidity and mortality (Sorino). For example, of those hospitalized with pneumonia, 20% to 40% have a parapneumonic effusion, and 5% to 10% of these parapneumonic effusions progress to empyema with approximately one-third of patients requiring surgical drainage of the pleural space (Najafi, Shen). Based on the 2016 National Hospital Care Survey, nearly 77,000 adult patients were hospitalized for pneumonia with 35% of inpatients dying either in the hospital or within 1 year of discharge (Peters). Those with pleural space infections often require additional procedures with increased length of hospital stay.

The three stages of parapneumonic pleural effusion include (1) simple exudative accumulation (2) fibropurulent with bacterial invasion of the pleural cavity, and finally, (3) the organized stage with the formation of scar tissue (Sorino). A parapneumonic effusion in the fibropurulent stage is usually defined as “complicated” since antibiotic therapy alone is not sufficient for its resolution and an invasive procedure (pleural drainage or surgery) is required. Biochemical features of a fibrinopurulent collection include a low pH (<7.2), low glucose level (<60 mg/dl), and high lactate dehydrogenase (LDH). Empyemas are often defined as frank pus aspirated from the pleural space, with some further defining positive gram stain and/or culture positivity as empyemas (Shen, Light, Davies).

The most recent BTS guidelines recommend that patients with frankly purulent, turbid/cloudy pleural fluid, or with a pH <7.2 on sampling should receive prompt pleural space chest tube drainage, although there is no consensus on optimal thoracostomy size in the absence of a randomized controlled trial (Davies). In a subanalysis of the Multicenter Intrapleural Sepsis Trial (MIST1) cohort, there was no increased efficacy with large-bore tubes compared with small-bore drains (Maskell).

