# **Target Accrual**

We plan to enroll a total of 96 patients who will be randomized with a 1:1 ratio to the interventions (regular saline flushing) or the control (standard of care) arms. We will generate the randomization sequence using a computer program.

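### The step from 76 evaluable patients to 96 enrolled multiplies up for the assumed losses; with both losses applied to everyone, 96 leaves about 72 to 73, a small shortfall

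*Protocol*

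**What the plan says.** The sample size paragraph under Statistical Considerations (Protocol) assumes median times to tube removal of "6 days in the SOC group and 5 days in the intervention group". The calculation is for a "two-sided Wilcoxon Rank-Sum test at a 0.050 significance level with a standard deviation of 1.5", checked by a "2000 Monte Carlo simulation assuming samples from a range of distribution such as Gamma, Lognormal, and Gumbel distributions". The result is that "Group sample sizes of 38 in each arm achieve 80% power to detect a median difference of 1".

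The paragraph then allows for losses: "Assuming a 10% withdrawal rate and 15% intrapleural enzyme therapy failure (which can prevent reaching the primary endpoint), we plan to enroll 96 Participants". Target Accrual repeats the total: "We plan to enroll a total of 96 patients", allocated 1:1. Neither section gives the inflation formula or says which patients the 15% is a share of.

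The analysis plans in the same section limit the primary rank comparison to patients whose tube was removed successfully. A patient who withdraws and a patient whose treatment fails are therefore both absent from the test for which the 38 per arm was calculated.

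**The concern.** To end with 76 analysable patients after a loss fraction d, one enrols 76/(1 − d). Enrolling 76 × (1 + d) falls short, because the loss is taken from the larger enrolled number. The figure of 96 fits the second formula and not the first. If so, the trial would have fewer patients in its primary comparison than its own calculation asks for, and the 80% attached to 38 per arm would not quite describe what 96 enrolled patients deliver.

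**Working it through.** **Inputs, all from Statistical Considerations:** two-sided α = 0.05; difference 1 day (medians 6 and 5); SD 1.5 days; 38 per arm; losses of 10% and 15%; 96 enrolled, 1:1.

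**Step 1. Does 38 per arm give 80%?** The exact t-test size for a difference of 1 with SD 1.5 and 80% power is 36.31 per arm. Dividing by the rank test's efficiency relative to the t-test under normal data, 3/π = 0.955, gives 36.31/0.955 = 38.02. The base size reproduces. Simulated Wilcoxon power at 38 per arm is about 80% or more for every distribution tried (table in Step 4).

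**Step 2. How is 96 reached from 76?**

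| Route | Arithmetic | Enrolled |
|---|---|---|
| Multiply up, losses added | 38 × 1.25 = 47.5, so 48 per arm | 96 |
| Multiply up, losses in sequence | 76 × 1.10 × 1.15 = 96.1 | 96 |
| Divide, losses in sequence | 76/(0.90 × 0.85) = 76/0.765 = 99.3 | 100 |
| Divide, losses added | 76/(1 − 0.25) = 76/0.75 = 101.3 | 102 |

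Only the multiply-up routes give 96.

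**Step 3. What does 96 leave if both losses apply to all enrolled?**
- Additive: 96 × 0.75 = 72, or 36 per arm.
- Multiplicative: 96 × 0.90 × 0.85 = 73.4, or about 37 per arm.

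The shortfall against 76 is 76 − 73.4 = 2.6 to 76 − 72 = 4 patients.

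**Step 4. What does that cost in power?** Simulated Wilcoxon power at α = 0.05, with each arm's distribution set to its own median and SD 1.5 (for Gumbel, a shift of 1 day):

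| Per arm | Normal | Gamma | Lognormal | Gumbel |
|---|---|---|---|---|
| 38 | 80% | 80% | 83% | 88% |
| 37 | 79% | 79% | 82% | 87% |
| 36 | 77% | 78% | 81% | 86% |

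The loss from 38 to 36 or 37 per arm is about 1 to 3 points. The protocol does not give its distribution parameters, and they matter slightly. If one curve is simply moved by a day, gamma comes out at about 79 to 81% and lognormal at about 82 to 83% for 36 to 37 per arm. Across both set-ups the range is about 77 to 81% for normal or gamma data and about 81 to 87% for lognormal or Gumbel data.

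**Step 5. What if the 15% applies to enzyme recipients only?** Let s be the share of patients given enzyme therapy; the protocol states no value.
- Additive: 96 × (0.90 − 0.15s). This equals 76 at s = (0.90 − 76/96)/0.15 = 0.72.
- Multiplicative: 96 × 0.90 × (1 − 0.15s). This equals 76 at s = (1 − 76/86.4)/0.15 = 0.80.

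At s = 50% there are 79.2 to 79.9 evaluable patients, and at s = 25% there are 82.8 to 83.2. On this reading 96 is enough up to a share of about 72 to 80%.

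**The case against.** The strongest reply concerns the denominator. The loss is described as failure of enzyme therapy, the inclusion criteria admit patients with or without it, and randomisation is stratified by its use. Read literally, the 15% could apply to recipients only, and Step 5 shows that 96 would then be sufficient over a wide range of shares. The text also says only that such failure can prevent the endpoint. This reply stands as a reason to state the denominator. It does not show that 96 was derived that way: no enzyme share appears anywhere, and only the all-enrolled reading leads to 96 from stated figures.

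The second reply is that the effect is negligible. The protocol's own simulation of 2000 runs carries a 95% margin of about 1.96 × √(0.8 × 0.2/2000) = 0.018, or 1.8 points, and lognormal and Gumbel power stays above 80%. The normal case is not among the protocol's named distributions. This stands, and it is why the point is minor.

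A reader might infer more than the document supports:
- *That the 80% power itself is wrong.* It is attached to 38 per arm, and it reproduces there.
- *That the 15% contradicts the Background*, which mentions "approximately one-third of patients requiring surgical drainage of the pleural space". That sentence describes surgical drainage in a general epidemiological account. The 15% is enzyme therapy failure among trial patients. The two quantities differ.
- *That the SD is far too small*, because the other cited series reports "5 days (3-7) in a study of 36 patients with no-flush strategy". The protocol does not say whether 3 to 7 is an interquartile range or a full range, so an SD of 2 or 3 would be a guess. The SD of 1.5 follows the cited study of patients with an infected pleural space (SD 1.53).
- *That dislodgement, malposition, kinking and death enlarge the shortfall by a known amount.* The protocol assigns these to a competing-risk model and gives no rates, so no figure can be computed.

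**Conclusion.** The inflation step is wrong as written on the only reading that yields 96 from the protocol's figures. Under that reading 96 enrolled gives 72 to 73 patients in the primary comparison, not 76, and dividing by the retained share would have given 100 to 102. Power falls by about 1 to 3 points: it sits around or just under 80% for normal or gamma data and remains above 80% for lognormal or Gumbel data.

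The conclusion rests on three assumptions: both losses apply to all enrolled patients, both remove a patient from the success-only comparison, and SD 1.5 with a 1-day difference is taken as given. If the 15% applies only to enzyme recipients, the shortfall shrinks or disappears, depending on a share that the protocol does not state. Severity is minor. The power calculation stands, and the trial is not materially underpowered on this account.

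**What to change.** Keep 96 and amend the sample size paragraph under Statistical Considerations:
- State the inflation formula and the denominator of the 15%.
- If the 15% is of all enrolled patients, say that 96 enrolled is expected to give about 72 to 73 evaluable patients (36 to 37 per arm), with about 77 to 81% power for normal or gamma data and about 81 to 87% for lognormal or Gumbel data. Give the distribution parameters behind the figures quoted.
- If the 15% is of enzyme recipients only, state the expected enzyme share and the evaluable number that follows from it.

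Enrolling 100 to 102 would also restore 76 evaluable patients, but a gain of 1 to 3 points does not require it. The cost of the preferred fix is a few sentences and a slightly less favourable stated power. Target Accrual needs no change if 96 is kept.

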# **Study Criteria**

**Inclusion Criteria**

- Patients with CPPE and empyema requiring chest tube placement as standard of care for inpatient management of their pleural space infection with or without intrapleural tPA/DNase therapy
- Age > 18 years old.

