# **Study Procedure**

Patients will be eligible for randomization immediately following and up to 24 hours after chest tube placement. As per the standard of care, patients with a chest tube require a chest X-ray after chest tube placement to assess the proper position of the chest tube. Chest X-ray and ultrasound images obtained at the time of chest tube placement will be reviewed and their information documented as baseline/ day 1. The study team will obtain a baseline assessment of the pleural effusion via ultrasound if no ultrasound images are available within 24 hours prior to chest tube placement).

Subjects will be randomly allocated into intervention (regular flushing) and control (standard of care/flush as needed) groups using computer-generated randomization just prior to starting the procedure.

The intervention groups will have sterile saline 20 mL flushed into their catheter by trained nurses or study team members every 6 ± 2 hours. If patients are receiving tPA/DNase (combined at the same time), each treatment will be considered one flush.

The control groups will have no saline routinely instilled into the chest tube. Instead, chest tube patency will be assessed at least once/day. If the chest tube is considered blocked (lack of tidaling, lack of fluid drainage, and presence of fluid on US exam), the chest tube will be flushed with 20 mL of saline if indicated. All patients in both arms will have -20 cm H2O at the atrium (-80 cm H2O at the wall) continuous suction applied to their drainage system at all times if tolerated.

A daily checklist will be completed by the research team to assess for chest tube blockages and ongoing need for the tube/potential removal of the catheter (see CRF).

On the day of chest tube removal, both the intervention group and control group will undergo a repeat chest X-ray. Post-chest tube removal ultrasound images will be obtained by the research team. Chest X-rays can be performed as portable semi-erect or PA and lateral based on the clinical judgment of the primary provider.

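### Randomisation is stratified by enzyme therapy use, but the primary test ignores the stratum and the factor has no time anchor: a possible gain in precision is given up, though planned power is not lost

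*Protocol*

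**What the plan says.** Statistical Considerations (sample size justification) sets the allocation rule: "To avoid an unbalance in randomization among groups, randomization will be stratified by intrapleural enzyme therapy use". It does not say whether use means given, ordered or planned, or by what time.

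Three other sections bear on timing:
- Study Procedure: "Patients will be eligible for randomization immediately following and up to 24 hours after chest tube placement".
- Inclusion Criteria admit patients "with or without intrapleural tPA/DNase therapy", with no rule on when it starts.
- Multistate Transition Model: "Patients could transition between states of patent, vs clogged and tPA/DNase free vs tPA/DNase therapy". In that model, "status will be assessed daily from randomization to treatment success, or failure".

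Statistical Considerations (analysis plans) gives the primary comparison, restricted to patients with successful removal. For normal data, "data will be analyzed via students t-tests comparing time from randomization until time to chest drain removal between the two arms". Otherwise, "For non-normally distributed data, the Wilcoxon rank sum test will be used for this comparison". Neither test has a stratum term. Covariate adjustment is mentioned only for the Cox model of time to failure of therapy or drainage, which is not the primary endpoint, and its covariates are not named.

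**The concern.** There are two linked problems.

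**Design and analysis do not match.** Balancing the arms within strata removes between-stratum spread from the true variability of the treatment difference. An unstratified test still counts that spread as noise. If the factor is prognostic, the test is conservative and precision is forgone.

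**The factor is not anchored in time.** A stratification factor must have a value when the allocation is drawn. Under the protocol's own state model a patient can be enzyme-free at randomisation and treated later. Later use may also depend on the arm: the trial is open label, each tPA/DNase treatment counts as a flush in the intervention arm, and the Background cites fewer fibrinolytic doses among patients given saline. If analysts later took actual use as the stratum or a covariate, they would be conditioning on a possible consequence of treatment.

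**Working it through.** **Inputs from the protocol (Statistical Considerations):** two-sided alpha 0.05, SD 1.5 days, medians 6 and 5 days, 38 per arm, 80% power by Wilcoxon.

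**Inputs assumed, because the protocol gives neither:** share on enzymes p = 30% or 50%; difference d between strata in removal time = 0 to 2 days.

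**Step 1. Reproduce the protocol's figure.** For two means, n = 2 × (1.96 + 0.8416)² × 1.5² / 1² = 35.3, so 36 per arm. Dividing by the Wilcoxon efficiency under normality, 36 / (3/π) = 37.7, so 38. In 10,000 simulated trials at 38 per arm the unstratified Wilcoxon has power 79.6% (normal), 80.4% (gamma), 83.2% (lognormal) and 87.8% (Gumbel). The 38 per arm reproduces, and it was sized for an unstratified test.

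**Step 2. Split the SD.** The 1.5 is used for an all-patient two-sample test and stands beside an all-patient SD of 1.53 from a cited study. It is therefore a total within-arm SD, and the within-stratum SD is w = √(1.5² − p(1 − p)d²). At p = 50% this gives w = √(2.25 − 0.25) = 1.41 for d = 1 and w = √(2.25 − 1) = 1.12 for d = 2.

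**Step 3. Compare the tests.** Simulation with 10,000 trials per cell, normal errors, 38 per arm, 1-day effect and exact balance within strata. Van Elteren weights are 1/(stratum size + 1).

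| Share on enzymes | d (days) | Power, unstratified | Power, van Elteren | Type I error, unstratified | Type I error, van Elteren |
|---|---|---|---|---|---|
| 50% | 0 | 80.2% | 79.8% | 5.1% | 5.2% |
| 50% | 1 | 81.0% | 84.1% | 4.2% | 5.3% |
| 50% | 1.5 | 83.0% | 89.9% | 2.2% | 5.1% |
| 50% | 2 | 84.7% | 96.5% | 0.8% | 4.7% |
| 30% | 0 | 79.8% | 79.4% | 4.6% | 4.7% |
| 30% | 1 | 81.3% | 83.6% | 3.9% | 5.0% |
| 30% | 1.5 | 82.4% | 87.8% | 2.9% | 5.3% |
| 30% | 2 | 84.5% | 93.6% | 1.4% | 4.8% |

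Gumbel errors give the same pattern from a higher base. At 50% on enzymes, power is 87.7% against 87.4% at d = 0 and 87.8% against 98.6% at d = 2.

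**Step 4. Check by formula.** The unstratified test uses SD 1.5 where the balanced design leaves w, so its type I error is roughly 2Φ(−1.96 × 1.5 / w). At p = 50% that is 2Φ(−2.08) = 3.8% for d = 1 and 2Φ(−2.63) = 0.9% for d = 2, in line with the table. A normal approximation to the stratified power, with 38 × 3/π = 36.3 effective patients per arm and SD w, gives 81.0%, 85.4% and 96.8% for d = 0, 1 and 2.

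**The case against.** Much of the case for leaving the plan alone is sound.

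- **Planned power.** The 38 per arm was calculated for the unstratified test and holds up. A reader might infer an underpowered trial by treating 1.5 as the within-stratum SD and adding stratum spread on top; that gives unstratified power of 77%, 65% and 45% for differences of 1, 2 and 3 days. The protocol does not support this. At 50:50 it would raise the total SD to √(2.25 + 0.25d²) = 1.58, 1.80 and 2.12. Most of the fall in power comes from that larger SD: with no strata at all, those SDs give 75%, 65% and 51%. The 3-day case cannot occur under a total SD of 1.5, because 0.25 × 9 = 2.25 uses up the whole variance.
- **Feasibility.** A reader might also infer that the stratification cannot be carried out. That follows only if use means any use while the tube is in place. Use given or ordered by allocation is a workable reading, so the defect is a missing definition. The state model is exploratory and does not define the stratum.
- **Validity.** A conservative test does not inflate type I error, and the stated aim of avoiding imbalance is met without a stratified test.
- **Size.** The protocol gives no difference in removal time by enzyme use. If there is none, nothing is lost. The simulation also assumes exact balance, which is not guaranteed among patients with successful removal.
- **Later harm.** Nothing says that later enzyme use will enter the primary analysis. Covariates may be named in an analysis plan that is not at hand.

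What stands is that the protocol itself names the primary test, and that test leaves out the randomisation factor. The factor's definition is needed at the first allocation, before any analysis.

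**Conclusion.** The point holds as a low-cost improvement and does not show an error in the sample size or a threat to validity. With total SD 1.5, 38 per arm, a 1-day effect and balanced strata, ignoring the stratum costs nothing if enzyme use is not prognostic. It costs about 2 to 3 points of power if the strata differ by 1 day, and about 9 to 12 points at 2 days. The unstratified test stays at about 80% power or better throughout, with type I error at or below about 5%. The share on enzymes (30% or 50%) and the stratum differences are assumptions, so the size of the gain is uncertain and its direction is not. The missing time anchor is a gap in definition that lets sites classify patients differently. The protocol does not show that the scheme is unworkable.

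**What to change.** In Statistical Considerations:

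1. Define the stratum as tPA/DNase given or ordered by the time of randomisation (yes/no), as entered on the randomisation form before allocation.
2. Replace the primary test with a van Elteren (stratified Wilcoxon) test on that recorded value or, if the data are judged normal, a linear model with arm and stratum.
3. Stratify the Cox and competing-risk models by the same recorded value.
4. State that enzyme therapy begun after randomisation is used neither as the stratum nor as an adjustment covariate.

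The cost is one form field, a few sentences and slightly more analysis work. The sample size and clinical care are unchanged. If the stratum turns out not to be prognostic, the change in power is negligible (79.8% against 80.2% in the 50% case, within simulation error).
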